### Interventions

All children will receive care typically provided by their usual treating organisation. Possible treatments include occupational therapy (e.g. goal-directed training, intensive bimanual therapy), prescription and use of equipment and /or BoNT-A injections. Some children may already have been prescribed a WHO. The WHO of those children allocated to the intervention group will be assessed to ensure it meets the intervention protocol, and adjusted if necessary. Those in the control will cease wearing their WHO. Due to the pragmatic nature of this trial, study duration and anticipated heterogeneity of the study sample and possible co-interventions, it will not be possible to standardise co-interventions, however a detailed log will be kept and efficacy/efficiency implications of a non-standardised comparator will be carefully assessed.

#### Treatment group

The treatment group will receive a custom-made serially adjustable rigid WHO to maintain the flexor compartment (muscles of the wrist, fingers and thumb) in a lengthened position to avoid shortening of the musculo-tendinous unit and other soft tissue. For children with unilateral involvement only one hand will be provided with an orthosis. For children with bilateral involvement, both hands will be treated if clinically indicated. The WHO may involve variations of a volar or dorsal/volar orthosis. Volar orthoses are placed on the palmar aspect of the hand and forearm; dorsal/volar orthoses have a component on the palm and a second, linked component on the back of the forearm. Both types of orthoses are designed and fabricated to achieve the same aims. Orthoses will be made of thermoplastic material, which when gently heated loses rigidity allowing it to be conformed to the child’s arm in the required position. On cooling, thermoplastics regain rigidity. Straps will be used to maintain the correct position of the child’s wrist/hand in the orthosis.

As there is no evidence to guide the optimal position to achieve with orthoses, wearing regimes or follow-up procedures, a national group of expert occupational therapists developed consensus-based guidelines to include in the study operating procedures. Rather than specify muscle and joint positions to achieve with orthoses, these guidelines provide principles to guide individualised positioning of the thumb, fingers and wrist in the orthosis based on the available passive range of motion of the flexor compartment and the relative contribution of wrist and finger flexor stiffness. Briefly, the thumb is positioned midway between full extension and abduction to maintain web space while avoiding metacarpal-phalangeal (MCP) joint hyperextension. Fingers are placed in a small amount of flexion (10–30° at MCP and inter-phalangeal joints) to prevent the hand slipping in the orthosis. The orthosis is then fabricated to maintain thumb and finger position with the wrist positioned in the orthosis to achieve stretch to the flexor compartment. Each WHO will be fabricated following a clinical assessment of the child’s range of motion and muscle tone. Therapists in participating study sites will fabricate the orthoses as part of their usual clinical duties to achieve an individualised position of the wrist and hand according to pre-determined principles outlined in the consensus-based guidelines.

To achieve a prolonged positioning effect, children will be asked to wear the orthosis for a minimum of 6 h for each 24 h period of the 3 years of the study [27]. Although night time wear is recommended, it may be appropriate for some children to wear the orthosis during the day: for instance, children with more severe impairments who do not use their hands to carry out activities and therefore for whom wearing a WHO is unlikely to impact on functional hand use. Children with bilateral upper limb involvement where both hands meet the criteria for wearing an orthosis will be asked to wear both orthoses each night. If sleep quality is compromised as a result of concurrently worn bilateral orthoses, recommendations will be to: (i) wear both orthoses each day; or (ii) wear one orthosis at night, the other during the day; or (iii) alternate wear of each orthosis on alternating nights.

The therapists who manufacture the WHO will monitor them in a manner consistent with usual clinical practice. Orthoses will be replaced or serially adjusted over time according to clinical indications to accommodate growth, ensure good fit and maintain appropriate positioning. Serial adjustment involves re-heating the orthosis and remoulding it to achieve an adjusted position. The altered position may be in a position of greater wrist/finger extension in response to improvement in range of motion or reduced muscle stiffness, or in a position of reduced wrist/finger position if range of motion decreases or muscle stiffness increases.

Families will be provided with verbal and written instructions for donning, caring for and cleaning the orthoses; wearing regimes and guidance for facilitating the child to wear orthoses. Consistent with usual clinical practice, families will be asked to contact the therapist who manufactured the WHO if any difficulties with orthosis wear arise such as rash, red marks, bruises, pain or difficulties wearing the orthosis for 6 h per 24 h period.

Fidelity of intervention will be considered in three ways. Therapists fabricating orthoses will be educated by study personnel regarding study requirements, orthoses fabrication and wearing principles, which will also be documented in the standard operating procedures provided to each participating therapist. Participating therapists will complete a questionnaire to record details of the design and fabrication of the orthosis and photograph each orthosis on completion of fabrication to provide study personnel with a digital image for evaluating orthosis manufacture against the pre-determined principles. These photographs will also enable assessment of the nature and design of orthoses used in the study. Data related to adjustments made to the WHO over the study period will also be collected. Finally, the frequency and duration that each child wears the orthosis will be recorded daily using a custom-designed application for Android and Apple mobile devices known as Therapy App (TherApp) (see *Intervention adherence* for details).

#### Control group

The control group will receive usual multidisciplinary care without a WHO. Prior to consenting, parents will understand that a child entering the study with a prescribed WHO and allocated to the control group will cease wearing it. Parents and children will be advised there is debate about effectiveness; the study will generate evidence to inform future practice. They will also be informed that children in either group could lose ROM during the trial period as this is the natural history of CP, and because of this, their child will be monitored closely throughout the 3 year study period.

#### Intervention – modifications

Children in either group could lose range of movement through the trial period as this is the natural history of CP. In addition, the trial will run for an extended period (3 years) during which growth and physical development will influence children’s outcomes. Both groups will, therefore, be carefully monitored for loss of range of motion over time.

Children will be monitored for the first 12 months following enrolment according to the study protocol and will not receive any modification to the intervention during this period. Children assessed at or after the 12-month time point who have lost ≥30° passive range of wrist extension or increased by ≥2 categories on the Modified Ashworth Scale, compared to baseline, in either group will be eligible for increased monitoring. This involves reassessment at 3-monthly intervals and may, in consultation with the child’s parents and treating team, involve either serial casting to regain range of movement and/or a referral for a surgical opinion. Casting is common clinical practice in children with CP to achieve increased passive range of motion over the short term [10].

#### Criteria for withdrawal

Withdrawal criteria, which apply to all children, have been specified *a-priori* to ensure child safety, quality of study data, and the ability to answer the research questions. Children who receive a diagnosis other than CP or their movement disorder evolves to dystonia without the presence of spasticity, will be withdrawn from the study and all data removed from analyses. Children who have a surgical intervention to the included upper limb or more than three episodes of casting as a modification to treatment during the course of the study may discontinue study treatment but will be followed until study completion and be included in the statistical analyses where possible.

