### Data collection methods for child-participants who exit prematurely

Children may exit prematurely from the study because of voluntary withdrawal or termination of WHO intervention due to harm (e.g. allergic reaction to materials). Participant retention will be supported within the study through provision of routine follow-up and regular feedback on child progress via the TherApp summary report that can be generated by parents throughout the trial. Where possible, all children will be followed to the study end point (3 years) so that data are available for analyses. Lack of adherence to the treatment plan will be recorded using TherApp and will not constitute a reason for withdrawal. Reasons for withdrawal from the intervention, or the study, will be recorded to assist with management of missing data and interpretation of results.

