### Statistical methods

The primary analysis will be by intention to treat. Comparison between the intervention and the control groups in the difference from baseline in the passive range of wrist extension (primary outcome) will be presented as the mean difference between the groups and its 95 % confidence interval, obtained using linear regression adjusted for the stratification factors of site and range of passive wrist extension at baseline. The regression model will be fitted using generalised estimating equations (GEE) to allow for the clustering of observations within children for those with both limbs in the study. To explore the effect of the adherence to WHO wearing schedule (i.e. a dose response relationship), a linear regression model will be fitted with compliance to treatment as a predictor and difference in the passive range of wrist extension from baseline to 36 months as the outcome, applied to all study participants. Again this model will be fitted using GEEs to allow for the clustering of limbs within participants. Evidence for an interaction between age and treatment, and between severity (Neurological Hand Deformity Classification) and treatment, will be explored by the inclusion of interaction terms in the linear regression models as well as GEE models. The analyses will be repeated, adjusting for potential confounders including occasions of upper limb BoNT-A injections and frequency of upper limb intervention. Analysis will also be undertaken using the ‘per protocol’ population excluding children who received surgical intervention or casting during the study. All data available from children who are withdrawn from the study prior to study completion will be used for analysis. Imputation of missing data will only be considered in the primary analysis if less than 10–20 % of the primary outcome is missing and will be undertaken throughout multiple imputation models.

Depending on whether data are continuous, categorical or dichotomous, the appropriate generalized linear model will be used to estimate the effect of treatment across the study period on secondary outcomes, again fitted using generalised estimating equations. All analyses will be adjusted for the same stratification factors as for the primary analysis and carried out on intention to treat and per protocol populations.

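### Deleting all data of randomised children who are re-diagnosed or evolve to dystonia conflicts with the stated intention-to-treat analysis, most clearly for the dystonia trigger

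*Protocol article*

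**What the plan says.** The section Criteria for withdrawal sets rules for both arms in advance: "Withdrawal criteria, which apply to all children, have been specified" beforehand. Two events trigger removal: "Children who receive a diagnosis other than CP or their movement disorder evolves to dystonia without the presence of spasticity". These children "will be withdrawn from the study and all data removed from analyses". The next sentence treats surgery to the included limb, or more than three casting episodes, the other way: those children may stop study treatment but "will be followed until study completion and be included in the statistical analyses where possible".

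The section Statistical methods says: "The primary analysis will be by intention to treat". It adds: "All data available from children who are withdrawn from the study prior to study completion will be used for analysis". Neither sentence carries an exception. The per-protocol set is defined there as "excluding children who received surgical intervention or casting during the study"; re-diagnosis and dystonia are not named.

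The section on children who exit prematurely says: "Where possible, all children will be followed to the study end point (3 years) so that data are available for analyses".

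**The concern.** For the same group of withdrawn children, one section says to use nothing and another says to use everything available. Two analysts following the article could form different primary analysis sets, and the choice could be made after results are known.

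The second issue is the kind of exclusion. Dropping a randomised child because of something that develops during follow-up gives up the protection of randomisation for that child. Spasticity is itself measured as a secondary outcome every 6 months, so the dystonia trigger depends on a state close to what the trial measures. If that state arises, or is recognised, at different rates in the two arms, or if the removed children differ in different ways, the estimated treatment effect shifts. Read literally, the rule also discards valid measurements taken before the change, and harms data, although the harms section collects these for all children.

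**Working it through.** **1. Do the two sections address the same children?** Both refer to children withdrawn from the study. The withdrawal section deletes all data of one class of them. The statistical section uses all available data from withdrawn children and names no class to be left out. They overlap and conflict for exactly the re-diagnosed and dystonia children.

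**2. Could the deletion be a per-protocol rule only?** No. The per-protocol exclusions are surgery or casting. The deletion is worded to cover analyses in general, so it reaches the primary analysis.

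**3. Is each trigger a change after randomisation?**
- *Dystonia without spasticity:* this is already an exclusion at entry (Child participants), and randomisation follows the baseline assessment (Randomisation). Evolution to that state is therefore a change after entry, at any point in 3 years.
- *Non-CP diagnosis:* a confirmed CP diagnosis is an entry criterion, and the Background describes CP as arising from disturbance in the foetal or infant brain. A later non-CP diagnosis will often correct an error that was present before randomisation.

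The article applies one rule to both.

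**4. The plan's own sample size.** Inputs from Sample size: difference 10°, SD 22°, two-sided 0.05, power 80%, 20% withdrawal and loss. The t-test calculation gives 76.95, so 77 per group. Inflation: 77 / 0.8 = 96.25, rounded up to 97 per group, or 194 in total. The stated figures reproduce, and this point does not affect them.

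**5. Power if children are deleted on top of the 20% loss.** The article gives no rate, so these are assumptions. Children left per arm = 194 × 0.8 × (1 − e) / 2; power by the normal approximation.

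| Assumed deleted share e | Left per arm | Power |
|---|---|---|
| 0% | 77.6 | 0.808 |
| 2% | 76.0 | 0.800 |
| 5% | 73.7 | 0.788 |
| 10% | 69.8 | 0.766 |

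**6. Possible shift in the estimate.** If k of 97 children in an arm are removed and differ by D from those kept, that arm's mean moves by (k / 97) × D. Assume removal in one arm only and D = 20°:
- k = 3: 3/97 × 20° = 0.62°
- k = 5: 5/97 × 20° = 1.03°

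This is about 6 to 10% of the 10° target. With removal in both arms, the shift in the difference is (e₁ − e₀) × D for a common D:
- 2% against 5%, D from 10° to 30°: 0.3 to 0.9°
- 2% against 8%, D from 10° to 30°: 0.6 to 1.8°
- equal shares and equal D: 0

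For scale, the design standard error is 22 × √(2/77) ≈ 3.5°.

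**The case against.** The strongest reply is that a specific rule, fixed in advance for two narrow triggers in both arms, qualifies a general sentence. On that reading the general sentence covers ordinary exits, such as voluntary withdrawal or stopping the orthosis for harm, and only a cross-reference or a label is missing. This has some force: the withdrawal section separates its two classes of children deliberately. But the statistical section states no exception. Even if the specific rule prevails, the resulting set is not the stated intention-to-treat set. Nor is this a detail that can simply be left to an analysis plan not shown here, because the article itself states two incompatible rules.

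A second reply is that re-diagnosis corrects an entry error. This stands in good part: a pre-specified, labelled modified set with blinded adjudication is defensible for that trigger. It does not extend to evolution to dystonia.

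A reader might also infer that unblinded staff decide who is removed. The article does not say so. It does not name who decides. Therapists providing the orthosis cannot be blinded, but blinded assessors rate spasticity every 6 months, so a loss of spasticity could also show in blinded data. All that can be said is that the article leaves open who decides and whether that decision is blinded.

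Finally, the primary outcome is passive wrist extension, not tone, and nothing in the article says that the orthosis changes the type of movement disorder. Bias needs a difference between arms, and the article neither shows nor excludes one.

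**Conclusion.** The contradiction is real and rests on the text alone. Following the withdrawal section produces a primary analysis other than the one stated. For evolution to dystonia this is a true post-randomisation exclusion on a tone-related state; for re-diagnosis the case is weaker.

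The numerical consequence is unknown and probably small. The 0.6 to 1.0° figure assumes 3 to 5 removals in one arm only, each deviating by 20°. None of these values comes from the article, and the shift vanishes if removals are alike in number and deviation in both arms. The power loss is minor: 0.808 to 0.788 at an assumed 5% deletion. A reader might infer a sizeable or known bias in the primary result; the documents do not support that. The reason to act is that the primary analysis set is ambiguous.

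**What to change.** In Criteria for withdrawal, replace the instruction to remove all data with a statement that data already collected, and any later data available, stay in the primary intention-to-treat analysis. Add a sensitivity analysis excluding children judged, blind to allocation, not to have had CP with spasticity at baseline.

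For the re-diagnosis trigger only, an acceptable alternative is a clearly labelled modified intention-to-treat set with blinded adjudication, provided that the sentence in Statistical methods on withdrawn children's data is qualified to match.

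The change concerns the use of data only, not whether a child stops study treatment. It costs about one sentence, plus the sensitivity analysis, and slightly more heterogeneity from a few children.

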#### Concomitant care

Children may participate in a range of upper limb interventions throughout the study according to usual multidisciplinary care, such as assistive technology or equipment and devices, upper limb BoNT-A injections, intensive bimanual therapy, early intervention, goal-directed training, home programs, modified constraint-induced movement therapy, or parent education/coaching [16]. Choice of concomitant interventions will be determined by the child’s family and treating team and will be recorded.

#### Intervention adherence

Adherence to the allocated intervention will be recorded using TherApp, which is the equivalent to an electronic diary. TherApp will be used in conjunction with a study-specific questionnaire to assist with measurement of WHO adherence, type of co-interventions and incidence of side effects from orthosis wear. Families of children with CP were consulted about the content, feasibility and implementation of TherApp.

Group allocation (concealed from the assessors) and personal details will be programmed into TherApp at the time of randomisation to ensure appropriate questions are asked about each child. Parents nominate the time for a daily and/or weekly reminder to be sent to their phone or device. For children in the intervention group, TherApp sends a daily prompt to parents requesting information on daily wearing duration and a weekly request for details on adverse events due to wearing orthoses, or any difficulties the child or family experience with wearing orthoses. TherApp will prompt parents to contact their child’s treating therapist if needed. We anticipate this will facilitate adherence to the provision of the WHO and contribute to treatment fidelity. If TherApp registers no response to the daily prompt, an automated email alert to the research assistant enables appropriate follow up. Parents of children in both groups will also receive a weekly TherApp request to record upper limb therapy received in the previous week. Data recorded on TherApp will be extracted prior to each assessment period and supplemented with 6-monthly parent interviews to record additional details about concomitant therapy in the preceding period.

In addition to the TherApp, a novel pressure sensor has been engineered to record the time orthoses are worn. Three sensors will be implanted in the contact-surface of the orthosis (under the thumb, fingers and wrist). The sensors developed for this study use wireless, blue tooth technology and have a sampling rate of 1Hz per second. This tiny device is printed on material safe for human consumption using 3-Dimensional printing technology to meet the combined requirements of accurate measurement, protection of skin integrity associated with device pressure and protection of the child from swallowing a small item. Data obtained from the sensor will be used to validate parent-report data extracted from the TherApp in a subset of participants.

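### Orthosis wear is quantified for the intervention arm only, so control exposure is undefined in a compliance model fitted to all participants

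*Protocol article*

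**What the plan says.** Under Intervention adherence, the article opens with a statement that covers either arm: "Adherence to the allocated intervention will be recorded using TherApp, which is the equivalent to an electronic diary". It adds a second instrument, also not restricted to one arm: "TherApp will be used in conjunction with a study-specific questionnaire to assist with measurement of WHO adherence, type of co-interventions".

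It then makes the app's content depend on allocation. Group allocation and personal details "will be programmed into TherApp at the time of randomisation to ensure appropriate questions are asked about each child". The wear question follows: "For children in the intervention group, TherApp sends a daily prompt to parents requesting information on daily wearing duration". What both arms share is a different item: "Parents of children in both groups will also receive a weekly TherApp request to record upper limb therapy received in the previous week". The app data are "supplemented with 6-monthly parent interviews to record additional details about concomitant therapy in the preceding period". Pressure sensors sit inside the orthosis and serve to validate the parents' app reports in a subset.

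Under Interventions, children who already have an orthosis and are allocated to control must give it up: "Those in the control will cease wearing their WHO". The Control group section repeats this.

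Under Statistical methods, an exploratory linear regression uses compliance to treatment to predict the 36-month change in passive wrist extension, "applied to all study participants". The value taken by a control child is not given. The per-protocol population leaves out children who had surgery or casting; orthosis wear by a control child is not among the exclusions.

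**The concern.** Some crossover is foreseeable. Some children will enter with an orthosis already prescribed. Those allocated to control are to go without it for 3 years. Their families are unblinded and have been told that range may be lost in either group. The article itself calls measuring and comparing co-interventions an important part of the trial, and wear of the study device by controls is the contamination that bears most directly on the comparison.

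Two things are at stake. First, the compliance model needs an exposure value for every child, but the article describes a source of that value for one arm only. Coding controls as zero would be wrong in exactly the children who crossed over. Second, if the primary comparison is null, the reader will want to know how far the two arms differed in actual wear, and the measures described answer that for one arm.

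**Working it through.** **1. Measures by arm, as described**

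| Measure | Intervention | Control |
|---|---|---|
| Daily wearing duration (app) | yes | not described |
| Weekly upper limb therapy (app) | yes | yes; orthosis wear not named |
| 6-monthly parent interview | concomitant therapy | concomitant therapy; orthosis wear not named |
| Study-specific questionnaire on orthosis adherence | yes | not excluded; content not shown |
| Sensor in the orthosis | subset, validates app reports | not applicable without a study orthosis |
| Compliance model | included | included; value not defined |

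**2. The plan's own sample size**

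Inputs from Sample size: difference 10°, SD 22°, two-sided alpha 0.05, power 80%, combined loss 20%.

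- Normal approximation: n = 2 × (1.960 + 0.842)² × 22² / 10² = 76 per group after rounding up.
- t-test: 76.95, so 77 per group, as stated.
- Loss: 77 / 0.80 = 96.25, so 97 per group and 194 in total, as stated.

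The allowance is for withdrawal and loss to follow-up; nothing is added for crossover.

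**3. Dilution of the intention-to-treat difference**

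Let c be the share of controls who wear an orthosis and f the fraction of the 10° effect that they gain. The expected difference is 10 × (1 − c × f). The document gives neither c nor f, so both are assumptions. With f = 1, 77 per group and SD 22°:

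| c | Difference | Power, t-test | Power, normal approximation |
|---|---|---|---|
| 0 | 10° | 80.0% | 80.5% |
| 5% | 9.5° | 75.9% | 76.4% |
| 10% | 9° | 71.3% | 71.8% |
| 20% | 8° | 61.1% | 61.7% |

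Only the product c × f matters. With half the benefit (f = 0.5), 10% crossover gives the 9.5° row and 20% gives the 9° row.

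These losses come from crossover happening. They would be the same whether or not it was recorded.

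**4. Effect of coding wearing controls as zero**

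Assumptions: 1:1 allocation; a true slope of 10° per unit of compliance; compliance uniform from 0 to 1 in the intervention arm; a share c of controls at full wear but coded x = 0.

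- E(x) = ½ × ½ = 1/4, E(x²) = ½ × 1/3 = 1/6, so Var(x) = 1/6 − 1/16 = 5/48.
- E(y) = 10 × (1/4 + c/2) and E(xy) = 10/6, so Cov(x, y) = 10 × (5/48 − c/8).
- Fitted slope = Cov / Var = 10 × (1 − 1.2c).

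This gives 8.8 at c = 10%, 7.6 at 20% and 6.4 at 30%. A simulation of the same set-up returned 8.80, 7.60 and 6.41. If crossed-over controls average half of full wear, c is replaced by c/2: 9.4 at 10% and 8.8 at 20%.

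Unlike the loss in step 3, this bias results from the coding, and recorded wear would remove it.

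**The case against.** The strongest reply is that the article does provide for adherence in both arms. It says that adherence to the allocated intervention is recorded, and for a control child the allocation is care without an orthosis. The questionnaire on orthosis adherence is not limited to one arm. The section on children who exit prematurely says that lack of adherence is recorded in the app. A detailed log of co-interventions is kept, concomitant care including equipment and devices is recorded, and the Data Monitoring Committee reviews protocol compliance. The exact wording of questionnaire items and the coding of a covariate normally belong in documents that are not shown. The compliance model is exploratory, and the primary analysis is by intention to treat in a pragmatic trial.

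Much of this stands. A reader might infer that controls are never asked about orthoses and that crossover goes wholly unmeasured; the text does not support that, because several records could reveal some wear. A reader might also take the power figures as the cost of not asking; they are not, since asking changes neither the difference nor the power. The full-benefit assumption is at the high end too, because the article describes orthoses as needing replacement or adjustment for growth and fit, and a retained device may not get that.

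What the reply does not remove is the mismatch within the article. It states that the app's questions depend on allocation, assigns the duration item to one arm, and then specifies a compliance model for both. A general statement that adherence is recorded does not give an amount of wear for a control child. The asymmetry has a sensible purpose, as the daily prompt is expected to support adherence, but that argues against a daily question for controls, not against an occasional one.

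**Conclusion.** The point holds in a limited form. As described, orthosis wear is quantified in the intervention arm and not in the control arm, and an all-participant compliance model therefore has no defined exposure for controls. Setting it to zero would bias the exploratory slope if controls cross over: from 10 to about 8.8 at 10% and 7.6 at 20%, on assumed crossover rates, full wear in those who cross over and uniform compliance in the intervention arm. The bias is smaller with partial wear.

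The intention-to-treat estimate is not invalidated; it remains an estimate of the effect of assignment. Crossover would pull it towards zero, and a record of control wear would show how much contrast in exposure lay behind a null result. No crossover rate is given, so the actual size is unknown. The unseen questionnaire may already contain a suitable item, in which case what remains is to say so and to define the coding.

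**What to change.** - Put the same orthosis-wear item to both arms at the existing 6-monthly interview: worn or not, which limb, and approximate hours over the period. Optionally add a short version to the weekly app request that control families already receive. If the questionnaire already asks this of controls, state it.
- In Statistical methods, define compliance for control children as their recorded wear, not an assumed zero.
- Report control-arm wear alongside the primary result.

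The cost is one interview item and, if wanted, one app item. The drawback is a possible reminder of orthoses to control families, which 6-monthly asking limits. It has to be done during follow-up, because wear cannot be recalled reliably after 3 years. Recorded wear removes the miscoding from the compliance model; it does not restore lost power.
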